##### Sensitivity analysis

Per-protocol analyses will be performed including only patients who received a prescription by those GPs who attended both training sessions. Additionally, two complete case analyses will be performed: one considering only those patients attended by GPs who completed the 7-month study period, and another using only non-imputed data.

To assess uncertainty in the output of the models, a sensitivity analysis will be performed without controlling the models for baseline covariates to assess their effect on the results of the cRCT [84].

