##### Inclusion criteria

Participating PC teams have to fulfil the following inclusion criteria: a) the PC team manager must be willing to participate in the study, commit to guaranteeing compliance with the ethical standards in the PC centre (see Ethics approval and consent to participate) and sign an informed consent for participation; and b) at least five GPs in urban areas or two GPs in rural areas who fulfil the inclusion criteria must be willing to participate at the moment of PC team inclusion. There is no minimum number of nurses required to participate.

To join the study, GPs and nurses have to fulfil the following inclusion criteria: a) to provide signed informed consent for participation in the clinical trial and the process evaluation; b) to attend the IMA intervention training entirely and c) not to anticipate a termination or interruption of employment (planning to change their place of work or taking sick/maternity/paternity leave) during the study period.

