As part of the implementation strategy of the IMA intervention, there are three inputs which are essential to achieve the intervention outcomes. First, top-down and bottom-up recruitment approaches are taken to increase professional engagement. Second, after the randomisation of the PC teams, healthcare professionals from the intervention group receive training on the IMA intervention, lasting 6 h. The training covers several aspects of non-initiation and other topics such as communication skills, health literacy and SDM. And lastly, decision aids have been designed to support the IMA intervention. These include one leaflet for each of the five pharmacotherapeutic groups and an *ad-hoc* website (available at: www.iniciadores.es). The leaflets will homogenise the intervention and provide tools to transmit the concepts of risk and benefit of the disease, treatment and alternatives. The leaflets contain a link to the website with a quick response code and this is considered a reliable source of information on CVD and diabetes. A full description of the intervention and its implementation strategy are described elsewhere [53].

Healthcare professionals in the control group will not receive training on SDM nor access to the decision aids and will be asked to provide usual care.

All participating professionals will receive a reinforcement session on the registry of clinical outcomes in the e-health records system and IMA-cRCT ethical standards.

PC team pairs will be randomised to the intervention and control groups and training sessions will be scheduled. Upon completion of training, each pair of PC teams will start the 7-month intervention in March 2022. The study period will last 7 months to account for healthcare professionals’ summer holidays, which last up to a month. During this time, the intervention will be applied to each patient meeting inclusion criteria. Figure 2 shows the trial flow-chart based on CONSORT guidelines.

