### Data collection

The SIDIAP database will be used to collect data for the evaluation of the effectiveness and cost-effectiveness of the IMA intervention. It implies the absence of any *ad-hoc* registry for the sake of the RCT.

SIDIAP gathers information from the electronic medical records of all patients seen by the public PC provider since 2010. This database provides information on patients’ sociodemographic and clinical data, including visits to primary care, health problems, sick leave periods, prescribed medicines, immunisations, laboratory results, clinical outcomes, and information on dispensed medication in any Catalan pharmacy [73]. All these records are dated.

The SIDIAP database is an encrypted, anonymised, secure database. It is managed by the Catalan Health Institute and CatSalut and provides real-world health data generated by the public health system in Catalonia to the scientific community under the legal and regulatory framework, following ethical principles, and maintaining transparency concerning the public program [74].

The SIDIAP database will be used to identify all patients that fulfil inclusion criteria to define the cohort of patients. They will be identified based on GP prescriptions. All variables will be collected for this cohort. All patient-related outcomes will be obtained from the encrypted and anonymised RWD databases. Patients’ personal information will not be provided to the research team. For each patient, data will be collected for the 12 months before the index prescription (for adjustment purposes) and from the subsequent 12 months (follow-up). Figure 3 depicts the observation periods in which the intervention is applied to patients. Information on healthcare professionals will be gathered through questionnaires at the training sessions [53].

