##### Quantification of uncertainty

Sensitivity analyses will explore the robustness of the results. First, to evaluate the uncertainty surrounding the estimation of the ICER, one-way sensitivity analyses will explore the impact of 1) the perspective, by considering the health system perspective, accounting only for direct medical costs; 2) the unit cost of productivity losses by calculating loss of productivity as the average daily wage in Catalonia [89]; 3) the analytical approach (per-protocol and complete case analyses); and 4) the costs considered, by including the cost of implementing the IMA intervention. The bootstrapping method will then be used to assess uncertainty in the sampling distribution of the ICER by using a minimum of 5,000 bootstraps. Bootstrapped pairs of cost and effect differences will be plotted on cost-effectiveness planes.

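### The per-protocol set is defined by training that only the intervention arm receives, so it has no usable control group, and the GP-completer set is mislabelled as a complete case analysis

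*Protocol article*

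**What the plan says.** The Sensitivity analysis section under Effectiveness defines the per-protocol set by GP attendance: "Per-protocol analyses will be performed including only patients who received a prescription by those GPs who attended both training sessions". It names no arm.

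The Intervention section says that, after randomisation, "healthcare professionals from the intervention group receive training on the IMA intervention, lasting 6 h". It does not say how many sessions this involves. For the other arm, "Healthcare professionals in the control group will not receive training on SDM nor access to the decision aids". One session is common to both arms: "All participating professionals will receive a reinforcement session on the registry of clinical outcomes in the e-health records system"; it also covers ethical standards.

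The Inclusion criteria for GPs and nurses require them "to attend the IMA intervention training entirely", again with no arm named.

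The same Sensitivity analysis section announces two complete case analyses. The first is "one considering only those patients attended by GPs who completed the 7-month study period"; the second uses only non-imputed data. On the source of outcomes, Data collection says: "All patient-related outcomes will be obtained from the encrypted and anonymised RWD databases".

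The economic evaluation reuses these sets. Item 3 of the one-way analyses in Quantification of uncertainty varies "the analytical approach (per-protocol and complete case analyses").

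**The concern.** A per-protocol comparison needs a membership rule that both arms can meet, or a method that does not need one. Here the rule rests on an event that happens after randomisation and can occur in one arm only.

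What is at stake is how the supporting results are read. The Strengths and limitations section says that there will be no hard data on fidelity and that no patient-level per-protocol analysis will be done. The GP-level set is therefore the only effectiveness analysis in the article that looks at the effect among GPs who took the training. If it came out larger than the intention-to-treat estimate, or gave a better ICER, a reader could not tell better delivery from better GPs.

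The GP-completer set raises a smaller issue. A complete case analysis handles missing data. This one removes patients because of something their GP did after randomisation, although the outcomes come from SIDIAP and do not depend on the GP staying in the study.

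**Working it through.** **1. What the per-protocol rule can mean.** Setting the Sensitivity analysis, Intervention and Inclusion criteria sections side by side leaves three readings:

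- *Both arms, literally.* Control GPs have no IMA training to attend. Even if one of the two sessions is the common session on outcome registration, they can attend only that one. The control set is empty and no contrast can be estimated.
- *Intervention arm only.* Attending GPs are compared with all control GPs, including those who would have missed the training had they been offered it.
- *Inclusion criterion b enforced in the intervention arm.* Every included intervention GP attended in full. The per-protocol set equals the intention-to-treat set in that arm, and the analysis is redundant.

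**2. The plan's own figure, to fix the scale.** Sample size section: 10% non-initiation, reduction of 3%, 80% power, 5% significance (taken as two-sided), ICC 0.01, 30 prescriptions per GP, 10% losses.

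- Per arm: (1.96 + 0.8416)² × (0.10×0.90 + 0.07×0.93) / 0.03² = 1,352.6; total 2,705.2.
- Design effect: 1 + 29×0.01 = 1.29, giving 3,489.8.
- Losses: 3,489.8 / 0.9 = 3,877.5, or 3,878 prescriptions; 3,878 / 30 = 129.3, or 130 GPs.

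This matches the stated 3,878 and 130, so the target is 3 percentage points (10% against 7%). The present point does not change that calculation.

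**3. Illustration of the one-arm reading, with no true effect.** Assumptions not in the documents: 10% or 20% of intervention GPs miss training; missing it correlates 0.5 with the GP's own non-initiation rate; the ICC, which the article gives for PC teams, applies to GPs.

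- Between-GP SD: √(0.01 × 0.1 × 0.9) = 0.03, or 3.0 points.
- Shift in the mean when the worst share is dropped: SD × φ(z) / share kept.
  - 10% dropped: 3.0 × 0.1755 / 0.9 = 0.58 points.
  - 20% dropped: 3.0 × 0.280 / 0.8 = 1.05 points.
- At correlation 0.5 these halve to 0.29 and 0.52 points.

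Simulation with 65 GPs per arm, 30 prescriptions each and beta-distributed GP rates agrees: about 0.3 points at 10% dropped and 0.5-0.6 at 20%. The false benefit is therefore about 0.3-0.6 points, or 10-20% of the 3-point target (0.3/3 and 0.6/3). In the same simulations the complier-average estimate shows essentially no bias.

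**4. Complier-average effect.** With training available in one arm only, the effect on the risk-difference scale is the intention-to-treat difference divided by π, the share of intervention prescriptions written by fully trained GPs. A 3-point difference becomes 3/0.9 = 3.33 at 90% trained and 3/0.8 = 3.75 at 80%. With π treated as fixed, the interval widens by 1/0.9 = 1.11 or 1/0.8 = 1.25.

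**5. The same scaling applied to the ICER.** With cost and effect differences on the same units, (ΔC/π) / (ΔE/π) = ΔC/ΔE. The share cancels and the result is the intention-to-treat ICER.

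**6. The GP-completer set.** The rule names no arm, so it filters both. The one-arm figures in step 3 do not apply to it.

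**The case against.** The strongest reply is that these are declared sensitivity analyses beside an intention-to-treat main analysis, for effectiveness and for the ICER alike. This is a condensed article that refers the full description of the intervention elsewhere, and the control-arm rule could be settled in an analysis plan. It stands that the primary analysis is intention to treat, and that the number of sessions may be defined elsewhere. But the article does fix a membership rule, and as worded no control GP can meet it.

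The size of the bias is also open to challenge. Neither the attendance rate nor the correlation comes from the documents, the ICC is for teams, and the bias is zero if criterion b is enforced. That stands: the figures are illustrative only. The 0.58 and 1.05 points before halving would require that exactly the worst GPs miss training.

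A reader might infer that the GP-completer analysis also selects the intervention arm, because intervention GPs carry more work and leave more often. The documents do not support this. The rule applies to both arms, inclusion criterion c screens out anticipated departures in both, and Strengths and limitations describes high workload among professionals in general. It mentions neither extra workload by arm nor leaving. Bias is possible if leaving differs by arm, but that is not shown.

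Two objections to the complier-average effect stand. It is the intention-to-treat result rescaled, so it is not an independent robustness check. It also assumes that allocation does nothing through untrained GPs, yet trained nurses and pharmacists may reach those GPs' patients.

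**Conclusion.** The per-protocol analysis is badly defined under every reading: impossible, selected on one side, or redundant. Which one applies depends on how the Inclusion criteria, Intervention and Sensitivity analysis sections are reconciled. Under the one-sided reading, about 0.3-0.6 points of spurious benefit is a reasonable illustration, resting on 10-20% non-attendance, correlation 0.5 and the team ICC applied to GPs.

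The GP-completer analysis has the wrong label and needs a caveat; no amount of bias can be attached to it.

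A reader might go on to infer that the trial's main result is undermined. This point does not show that: the sets at issue support the intention-to-treat analysis and do not replace it. The correction should be made, but the primary conclusion does not depend on it.

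**What to change.** - **Reconcile the sections.** Define the two training sessions, and state for each arm what inclusion criterion b requires, consistently across Inclusion criteria, Intervention and Sensitivity analysis.
- **Initiation and adherence.** Replace the per-protocol analysis with a complier-average effect: randomised group as instrument, full training of the prescribing GP as treatment received, all control prescriptions kept, and clustering by PC team. Prescriptions of untrained intervention GPs must also stay in, or there is nothing to scale.
- **State its limits.** The interval is wider. Trained nurses and pharmacists may breach the exclusion restriction, so the estimate may be somewhat too large.
- **ICER, item 3 of Quantification of uncertainty.** Drop the per-protocol ICER, or label it a non-randomised comparison. Do not substitute a complier-scaled ICER.
- **Complete case analyses.** Rename the 7-month analysis a post-randomisation GP-completer sensitivity analysis that may be biased if leaving differs by arm. Keep the non-imputed-data analysis as the only complete case analysis.

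The cost is wording and one extra model. The attendance data are already needed for the planned analysis, and the sample size does not change.

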#### Economic evaluation

The economic evaluation of the IMA intervention will consist of two analyses: first, an economic analysis to assess the cost-effectiveness of the IMA-cRCT for the duration of the trial and, second, an economic model to extrapolate the results of the 12-month cRCT and estimate the long-term cost-effectiveness of the IMA intervention. The primary analysis, either for the trial or the model, will use an intention-to-treat approach; the key outcome will be the incremental cost-effectiveness ratio (ICER) of the IMA intervention compared to usual care.

The ISPOR guidelines on good research practices for cost-effectiveness analysis (CEA) alongside clinical trials [85] will be followed in the economic evaluation of the IMA intervention to improve its quality and therefore increase the value to decision-makers.

##### Short-term cost-effectiveness

The short-term CEA will consider 12-month individual patient-level clinical outcomes and costs from all participants included in the IMA-cRCT. The main CEA will be presented from a limited societal perspective [86].

##### Costs

For the analysis of the impact of the IMA intervention on total costs, costs from the limited societal perspective will be estimated by adding direct medical costs and indirect costs (i.e. productivity losses) [86].

Healthcare and social service use will be converted to monetary costs by multiplying each item by its tariffs, published in the Official Government Bulletin [87]. Medication cost paid by patients and by the Spanish National Health System is registered in the SIDIAP database. Sick leave will be used as a proxy for productivity losses, converted to monetary costs by using the minimum daily wage in Spain [88]. The price year used will be the most recent year for which official unit costs are available. Unit costs will be updated according to the 2023 Spanish Consumer Price Index (IPC). The cost of the IMA intervention will be calculated as part of the cost of study implementation, as described elsewhere [53], and used in a sensitivity analysis.

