#### Cost-effectiveness outcomes

All cost data will be collected from the SIDIAP database and will be understood to cover the use of healthcare and social resources and sick leave for each patient, 12 months before and after the index prescription.

The following direct costs will be considered: visits to PC (GP and nurse; on-site and home visits) and emergency room (PC or secondary care); referral to secondary care; hospital admissions (inpatient admissions and outpatient consultations); use of social care services (such as visits to the social worker); and outpatient diagnostic tests and medication use. Indirect costs considered include productivity losses (as sick leave).

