##### Cost-effectiveness analysis

The difference in costs between groups will be estimated using multilevel generalised linear regression models with total costs as dependent variables. Due to the unpredictability in the distribution of costs, various distribution families and link functions will be tested and Akaike and Bayesian information criteria (AIC and BIC) will be used to choose the model with the best fit (usually the gamma distribution with a logistic link). The models will be controlled additionally for baseline costs (those incurred in the 12 months preceding the index prescription).

The difference in effects between groups will be estimated with multilevel regression models. For CVR reduction, multilevel linear regression models adjusted also for baseline CVR will be used. For secondary analyses, the difference in the probability of initiation and secondary adherence between groups will be estimated using a multilevel logistic regression with medication initiation or secondary adherence as the dependent variables.

The ICER will be calculated by dividing the difference in costs between groups by the difference in effects between groups.

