### Strengths and limitations

Complex interventions, like the IMA intervention, contain several interacting components and present practical and methodological difficulties, such as standardising its design, adapting it to the local context and translating it into real practice [52]. We are aware that there may be many barriers that can hinder the implementation of an IMA intervention. The main ones are described below, together with the strategies for overcoming them.

Firstly, the workload of healthcare professionals is high, which could restrict their participation in the study and limit the fidelity of healthcare professionals to the intervention. To reduce the existing barriers to the participation of healthcare professionals, we involved healthcare professionals in the design of the IMA intervention and developed a brief and acceptable intervention tested in a pilot study [54], which is expected to increase fidelity to the intervention. Additionally, healthcare professionals from the intervention group will receive monthly newsletters with reminders and information related to the intervention. Simplified means of obtaining patients’ informed consent is also expected to facilitate the participation of GPs (see Ethics approval and consent to participate). Finally, all healthcare professionals will receive economic compensation for the time devoted to the training for the IMA intervention. Nevertheless, the top-down approach may limit the recruitment of healthcare professionals.

Periodic feedback will be provided throughout the study to remind healthcare professionals about the study and intervention. Since there will be no hard data to assess the fidelity of healthcare professionals to the intervention, they will be asked to self-report this during the process evaluation; per-protocol analyses under the perspective of the patients receiving the intervention will not be conducted.

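### The main within-trial cost-effectiveness analysis leaves the delivery cost of the IMA intervention out of the base case and adds it only as a one-way sensitivity analysis

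*Protocol article*

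**What the plan says.** The Economic evaluation section makes the ICER of the IMA intervention against usual care the key outcome. Under Short-term cost-effectiveness: "The main CEA will be presented from a limited societal perspective". The Costs section defines the total for that perspective as direct medical costs plus productivity losses.

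The Cost-effectiveness outcomes section states that "All cost data will be collected from the SIDIAP database". Its list of direct costs runs from "visits to PC (GP and nurse; on-site and home visits) and emergency room (PC or secondary care); referral to secondary care; hospital admissions" to social care, diagnostic tests and medication. Training, leaflets and website are not on it.

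The intervention's own cost appears in two places. In Costs it is to be "calculated as part of the cost of study implementation, as described elsewhere [53], and used in a sensitivity analysis". In Quantification of uncertainty it is the last of four one-way variations: "4) the costs considered, by including the cost of implementing the IMA intervention".

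The Intervention section describes 6 hours of training for intervention-arm professionals, leaflets for the drug groups and a website. The control arm gets neither the shared decision-making training nor the decision aids. Strengths and limitations adds that "all healthcare professionals will receive economic compensation for the time devoted to the training for the IMA intervention".

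**The concern.** An ICER meant to inform adoption should carry the cost of the thing adopted. Here the base case counts what happens downstream of the intervention (visits, admissions, drugs, sick leave) but not what it takes to deliver it. Because the missing cost falls on one arm only, it does not cancel in the difference between arms.

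This also sits badly with the trial's stated purpose. The Discussion describes the burden of training and decision-aid development as high, and says the study will evaluate whether spending in the short term is recovered later. A main analysis that omits the spending cannot answer that question. If the true cost difference is small, the omission could decide whether the headline reads as cost-saving or as cost-increasing.

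**Working it through.** **1. Is the cost really outside the base case?** Costs assigns it to a sensitivity analysis. Quantification of uncertainty describes a variation that consists of adding it, which makes sense only if the base case lacks it. The direct-cost list does not contain it. The three places agree, and no reason is given. Read literally, the other one-way variations (perspective, wage, analysis population) would also be run without it.

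**2. Direction.** Let ΔC be the planned base-case cost difference (intervention minus control), ΔE the effect difference, c > 0 the delivery cost per patient in the intervention arm, and λ the willingness to pay per unit of effect.
- Planned ICER = ΔC/ΔE; with delivery cost = (ΔC + c)/ΔE. The shortfall is c/ΔE, an understatement when ΔE > 0.
- Planned net benefit = λΔE − ΔC; with delivery cost = λΔE − ΔC − c. It is overstated by c whatever the sign of ΔE. (The article plans net benefit for the long-term model; it is used here only to show direction.)
- If −c < ΔC < 0, the base case shows a saving where the full cost difference is positive.

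**3. Size in GP time.** Inputs: 6 h of training (Intervention); 65 GPs per arm, 3,878 prescriptions in total, and 30 new prescriptions per GP in 6 months (Sample size); a 7-month intervention period (Design).
- GP training: 65 × 6 = 390 h.
- Intervention-arm prescriptions from the sample size: 3,878/2 = 1,939. Then 390/1,939 = 0.201 h = 12.1 min each.
- Scaled to 7 months: 30 × 7/6 = 35 per GP, and 65 × 35 = 2,275. Then 390/2,275 = 0.171 h = 10.3 min each.

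The article explains the seventh month by summer holidays, so either denominator is defensible; hence 10 to 12 minutes.

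**4. What that means per unit of effect (illustration).** The article assumes a 3% reduction from 10% non-initiation. Reading it as 3 percentage points reproduces the stated sample size:
- n per arm = (1.960 + 0.842)² × (0.10 × 0.90 + 0.07 × 0.93)/0.03² = 1,352.6
- design effect = 1 + 29 × 0.01 = 1.29
- total = 2 × 1,352.6 × 1.29/0.9 = 3,878

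With ΔE = 0.03, the GP training time left out is 6/30/0.03 = 6.7 h per additional initiation, or 6/35/0.03 = 5.7 h.

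**5. Euros (assumed values only).** The article gives neither c nor a wage for professionals. The addition to the ICER, c/ΔE, would be:

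| Assumed c per prescription | ΔE = 0.01 | ΔE = 0.03 | ΔE = 0.05 |
|---|---|---|---|
| €1 | €100 | €33 | €20 |
| €5 | €500 | €167 | €100 |
| €10 | €1,000 | €333 | €200 |
| €20 | €2,000 | €667 | €400 |
| €50 | €5,000 | €1,667 | €1,000 |

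These are euros per additional initiated prescription. In the Cost-effectiveness analysis section, cardiovascular risk reduction comes first and initiation belongs to the secondary analyses. The table therefore does not show how far the risk-based ICER would move.

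**The case against.** The strongest defence is that nothing is hidden. The cost will be calculated, an ICER including it is prespecified, and readers will see both. No effectiveness estimate is touched. That stands, and it limits the harm. It does not settle the matter, because the figure presented as the main result would still be the one without the delivery cost.

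The size is also uncertain. The 10 to 12 minutes load all the training onto trial-period prescriptions. If trained GPs go on using the skills, the cost per prescription falls. No cost difference is available for comparison, so whether the effect is material cannot be shown from the article.

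A reader might infer more than the text supports:
- *The intervention is treated as free.* It is not. Extra GP or nurse visits and extra dispensing that it causes are in the base case. Training and decision aids are what is missing.
- *The omission always favours the intervention.* On the ICER scale this needs ΔE > 0. It is general only for net benefit.
- *The bootstrap planes carry the same bias.* The article does not say which cost definition the bootstrap uses.
- *The long-term model omits the cost too.* Economic model and One way-sensitivity analysis mention annual care costs and variations in costing, and are silent on this item.

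**Conclusion.** The concern holds for the within-trial analysis. The base-case incremental cost is understated by the delivery cost per patient, and the headline ICER by c/ΔE if the intervention improves the outcome. The article's figures put GP training alone at about 10 to 12 minutes per intervention-arm prescription. Nurse and pharmacist training, leaflets and website come on top. The euro size cannot be derived from the article and may be small per patient. The conclusion rests on c being positive and borne by one arm, both of which follow from the Intervention section.

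A separate, minor wording slip: the Cost-effectiveness analysis section gives as its usual cost model "usually the gamma distribution with a logistic link". A logit link confines the mean to between 0 and 1 and cannot serve for costs in euros; a log link is evidently meant. Family and link are to be chosen by AIC and BIC and the phrase is only an example, so no result depends on it.

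**What to change.** - **Costs:** include the delivery cost in base-case total costs of the within-trial analysis. Value training time once, through the compensation paid or through a wage; the compensation is for that time, so counting both would double count. Add decision aids and website upkeep.
- **Costs:** because the amount is to be calculated within the study implementation costing, separate delivery from research-only and one-off development costs.
- **Costs:** state how lump sums are allocated to intervention-arm patients. Outcomes and costs are analysed per patient, patients can enter more than once, and they can use any pharmacy, so pharmacist training in particular needs a rule.
- **Quantification of uncertainty:** make exclusion of the delivery cost the fourth one-way variation, and build the main bootstrap plane on the new base case.
- **Economic model:** state that its base case treats the cost in the same way.
- **Cost-effectiveness analysis:** replace the logistic link with a log link.

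The cost is already due to be calculated, so the extra work is a small allocation exercise. The price is a slightly less favourable ICER if the effect is positive. The change should be made before the economic analysis.
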